### Ethical considerations

The study is conducted according to the principles of the Declaration of Helsinki (2013) and in accordance with the Medical Research involving human subjects act (WMO) and other guidelines, regulations, and acts (AGV/WGBO). The study is also conducted according to the codes of conduct for minors (available on the Central Committee on Research Involving Human Subjects (CCMO) site and accepted by the Board of the Dutch Society for Pediatric on May 21, 2001).

There are no known risks or adverse effects to ultrasound imaging, when the intensity is limited to the current Food and Drug Administration (FDA) regulations as is the case in this CE notified device. There are no additional serious risks expected for participants.

Potential burden for the individual subject is mainly time consummation (regular hospital visits/telephone contact with the health care provider) which is not different between the groups and part of standard care in urotherapy. In addition, discomfort or social embarrassment might be experienced by the subjects wearing the SENS-U of SHAM device (despite the fact that only a discrete notification is given). Potential benefit for the individual subject is improvement of their complaints. Whilst it remains unclear if addition of the SENS-U to urotherapy remains (cost)-effective, in the future, other subjects might benefit from the outcomes of this study. Adverse events and serious adverse events will be recorded and managed according to previously mentioned principles, regulations, and guidelines.

Subjects can leave the study at any time for any reason if they wish to do so without any consequences. The investigator can decide to withdraw a subject from the study for urgent medical reasons, like skin problems or severe behavioral/social problems that are incompatible with protocolled urotherapy. Subjects discontinuing the study receive regular follow-up and treatment otherwise for their LUTD.

### Data management

Data from the study participants will be handled confidentially at all times according ICH-GCP regulations. The original signed informed consent forms will be kept in a binder in a locked closet in a locked room of all participating centers. After written consent, per center, each subject will receive a unique identifier, after which members of the research team will extract all necessary clinical parameters from the electronic health records into an electronic case report form (eCRF) of CASTOR EDC. The eCRF contains data items as specified in this research protocol. Access to the eCRF is password protected and specific roles are assigned (e.g., study coordinator, investigator, monitor, etc.). All study protocols, CASTOR generated data, statistical analyses, and reports are stored in a secured Digital Research Environment (AnDREa), and access is password protected and assigned to research members only. At the end of the study, all generated (meta)data will be stored as a proprietary format in a secured data archive called DANS EASY. In order to reproduce the study findings and to help future users to understand and reuse the (meta)data, all changes made to the raw data, including analysis steps, will be documented in an data management analysis plan available on request. Thus, the secure DRE will serve at the end of the study as a data package. More details, including the state of FAIRness, can be found in the data management plan. https://dmponline.dcc.ac.uk/public_plans?page=1&search=additional.

### Data monitoring/auditing

This study is monitored by independent, qualified monitors which are authorized to verify the accuracy and integrity of the data, conduct of the trial, compliance with the protocol, standard operating procedures, good clinical practice, and other regulatory requirements.

They have no competing interests and function independent of the sponsor. According to a predefined monitor plan (available on request) initiation visits, follow-up visits and close out visits are part of the monitoring.

The principal investigators of all participating centers are part of the project management team and meet every 6–8 weeks to discuss the conduct of the trial and are responsible for the correct execution of the study at their site according to the protocol. In addition, the principal investigator of the coordinating center and the project leader have weekly meetings and are responsible for obtaining and maintaining overall authorization of the study and (substantial) amendments to the protocol. The coordinating center accounts for financial affairs and communicates with external parties (Medical Ethical Committee and ZonMw).

This study was funded by an independent self-governing organization (ZonMw) with an independent trial steering committee of 21 members. They were closely involved during the initiation of the project (grant allocation) and will continue to monitor the project till the end. At set intervals, progress reports are required and reviewed. Yearly progress reports are also required and reviewed by the Ethics Committee of Arnhem/Nijmegen.

Day-to-day support is provided by trial offices at each site which help the site specific principal investigator.

### Patient public involvement

A patient advisory board was set up, including parents of each participating center. They were involved from the start. This board gives solicited and unsolicited advice throughout the initiation, design, and progress of the study and implementation of the SENS-U afterwards if the SENS-U turns out to be cost-effective. At least two times a year—and more often if indicated—the board meets with the principal investigator of the coordinating center and the project leader. Reimbursement of costs and deployment are covered.

### Data analysis and publication

Data are analyzed according to an intention to treat analysis, without replacement of individuals who withdraw during the study, using a Poisson or linear mixed model (depending on the distribution of the main outcome) with all available study time-points used. In case of premature withdrawal, last available data will be used. A correction for baseline, center, age, cumulative dose of antimuscarinics (if applicable), and adherence/drop-out will be performed. A random intercept and slope will be estimated if model fit allows for it. Descriptive statistics are used to analyze subjective improvement according to child and parents, adherence to treatment and to the SENS-U/SHAM device, user friendliness and (dis)comfort of the SENS-U/SHAM, and other previously mentioned outcome objectives. The data generated by the validated PIN-Q and EQ-5D-5L instruments are transformed and interpreted according to instructions given for each questionnaire [18–20]. A mixed model analysis is done to detect any difference in outcome between the three groups. Subgroup analysis will be done to study the effect of treatment in different age-groups, center, gender, socio-economic background, and in case of psychiatric co-morbidity. No interim analysis is done as no significant risks or benefits are expected for one of the three different study groups.

The results are shared with relevant fora and data will be presented at international conferences and published in peer reviewed medical journals without restrictions.

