**Methods/design:**

This is a multi-center clinical superiority parallel-group randomized controlled trial including a total of 480 children. Participants between 6 and 16 years of age with functional DUI in which urotherapy is offered as the next treatment of choice are eligible. Four centers, two academic hospitals, and two general care (peripheral) centers are participating. Participants will be randomized at a 1:1:1 ratio into three groups: urotherapy (care as usual), urotherapy with the SENS-U added for 3 consecutive weeks throughout the training, or urotherapy with a SHAM device for 3 weeks. The primary outcome is number of wetting accidents per week after 3 months of training, compared between the SENS-U and the SHAM device. The magnitude of the placebo effect will be assessed by comparing the results of the SHAM group versus the control (care as usual) group.

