## Background

Lower urinary tract dysfunction (LUTD; functional incontinence) is a common condition with a prevalence up to 21% in 6–17-year-old children [1, 2]. It is associated with an impaired quality of Life, lower self-esteem, and social stigmatization [3, 4]. Children rate “wetting their pants in class” repeatedly in the top 5 of most stressful life events [5].

According to the International Children’s Continence Society (ICCS), urotherapy is the first treatment of choice for functional urinary incontinence [6]. Urotherapy uses non-pharmacological, non-surgical methods and focuses on behavioral interventions, largely based on cognitive-behavioral psychotherapy. The main aim of urotherapy is to achieve the normalization of the micturition and bowel pattern and to prevent further functional disturbances by repeated training [6]. Studies on the effectiveness of urotherapy report success rates between 40 and 70% [7]. A meta-analytic evaluation of incontinence interventions reported a success rate of urotherapy of approximately 54% within 1 year of treatment (complete dry in 44% and a maximum of one wet episode a week in 10%). The overall reported spontaneous recovery rate in children is 15% per year [7–9].

Additional tools often used in urotherapy are voiding diaries, frequency voiding charts (FVC), uroflowmetry, and alarm interventions [6]. The voiding diary is used as a feedback tool that makes children aware of their voiding behavior. An alarm system gives either feedback when wetting accidents has occurred or notifies the child a set interval to go to the toilet. These systems do not teach the child the interpretation of the bladder sensation that precedes wetting accidents. A new wearable bladder sensor recently became available, the SENS-U. This is a relative small, wireless ultrasonic sensor, which continuously monitors bladder filling and alarms the child when it is time to void. The SENS-U may increase children’s awareness of the sensation of a full bladder. It can be personalized by adjusting the percentage of bladder filling at which it sends an alarm, based on the child’s own bladder capacity and FVC [10–12]. This teaches children which bladder sensation corresponds to a nearly full bladder and when it is time to void.

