## Methods/design

### Study design and setting

This study is multicenter clinical superiority parallel-group randomized controlled trial, designed according to the SPIRIT 2013 checklist (Additional file 1). The final study protocol version 6.0, December 2021, was approved by the Ethics Committee of Arnhem-Nijmegen in the Netherlands (NL 78403.091.21) and registered in ISRCTN44345202 (March 2022).

Participating centers in the Netherlands are the Wilhelmina Children’s Hospital in Utrecht, the Radboudumc Amalia Children’s Hospital in Nijmegen, Isala Clinic in Zwolle, and TOP voor kinderen in Arnhem. The first two are academic referral centers, the latter peripheral centers. The study will be conducted from June 2021 to June 2025. First-, second-, and third-line centers are participating in this study with the intention to select not only therapy-resistant children referred to third-line centers but also children seeking medical attention for functional DUI at the start of their condition.

The study consist of three parallel arms: urotherapy (care as usual), urotherapy with addition of a SENS-U device, and urotherapy with addition of a SHAM device. Outcomes parameters are measured at baseline, after the end of 3-week training with or without SENS-U/SHAM, after 3 months at the end of urotherapy, and 6 months after start of the training. Total study duration is 4 years. Individual study duration for subjects is 6 months.

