### Primary outcomes and secondary outcomes

The main study outcome is the number of wetting accidents per week after 3 months of urotherapy. Secondary outcomes are number of per-post wetting accidents classified further according to the ICCS standards in complete response (100% reduction of complaints), partial response (50-99% reduction), and no response (less than 50% reduction) [14]. Furthermore, magnitude of the placebo-effect contribution (SHAM versus control) will be assessed next to subjective improvement of symptoms according to child and parents, number of wetting accidents per week during follow-up 6 months after baseline, cost effectiveness, and change in FVC parameters (average, minimum, maximum voided volumes corrected for bladder capacity for age (EBC) between baseline (T0), after 3 months (T3), and after 6 months (T6). Change in disease specific quality of life as measured by the PINQ is also compared between T0, T3, and T6.

Other objectives include adherence to urotherapy and adherence of wearing the SENS-U/SHAM, patient experiences of user friendliness/(dis)comfort of the SENS-U/SHAM device, occurrence of urinary tract infections and constipation, and uroflowmetry curves.

Adherence to urotherapy is defined as number of failed contact moments/number of expected contact moments during the 3 months training. The SHAM and SENS-U measure the number of days actually worn. Adherence of wearing the SENS-U/SHAM is measured as a proportion (number of days not worn/total number of days used in training).

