### Sample size

The sample size calculation is based on detecting a difference between the intervention (SENS-U) group and the placebo (SHAM) group at the 3 month endpoint on the primary outcome number of wetting accidents per week. Following the ICCS guidelines, most published studies categorize the number of “wetting accidents per week” in three categories (complete response, partial response, no response) [14]. Information about the initial data used for the categorization (i.e., the number of wetting accidents) is seldom available. Therefore, our sample size calculation is based on a Fisher’s exact test with the known proportions. This will give a slight overestimation of the necessary sample size when analyzing wetting accidents per week, since this latter variable has more variance.

In this calculation, we assume the SHAM condition to be comparable to urotherapy using currently existing wearable alarm treatments (timer watch, pants alarm) [13, 15]. Success rate vary between 53 and 74%, depending on type of referral center [16, 17]. Since this study includes first- to third-line centers, we use an average success rate of 64% to be the estimate success rate of the SHAM condition in our sample size calculation. In addition, we expect at least a 15% additional effect in the intervention (SENS-U) group, based on current clinical experiences with the SENS-U [12].

With a Fisher’s exact test for two independent proportions, one-sided *a* = 0.05, power = 0.80, 64% success in the SHAM group, and 79% success in the SENS-U group, 124 children per group are needed. The one-sided alpha will provide a slight underestimation of the sample size. Given the previous assumption that our sample size calculation result in slight overestimation of the sample size, we presume that the overestimation and underestimation will cancel each other out. With 23% lost to follow-up, we need 160 children per group, 480 children in total.

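### The primary model is chosen from the data between Poisson and linear, and the Poisson option is anti-conservative if weekly accidents vary more than Poisson within a child

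*Protocol article*

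**What the plan says.** Under Primary outcomes and secondary outcomes, the protocol article states: "The main study outcome is the number of wetting accidents per week after 3 months of urotherapy". The abstract names the comparison: "number of wetting accidents per week after 3 months of training, compared between the SENS-U and the SHAM device".

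Data analysis and publication gives the method: an intention-to-treat analysis "using a Poisson or linear mixed model (depending on the distribution of the main outcome) with all available study time-points used". It adds: "A random intercept and slope will be estimated if model fit allows for it". Covariates are listed as follows: "A correction for baseline, center, age, cumulative dose of antimuscarinics (if applicable), and adherence/drop-out will be performed". Study design and setting gives the schedule of outcomes: "measured at baseline, after the end of 3-week training with or without SENS-U/SHAM, after 3 months at the end of urotherapy, and 6 months" (the last counted from the start of training). Baseline is thus itself one of the measurement times.

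No rule is given for choosing between the two models. No mean, SD or dispersion of weekly accidents appears anywhere; the Sample size section says that such count data are seldom available. The nearest hint is in the Background, where a meta-analysis of urotherapy within 1 year is reported as "complete dry in 44% and a maximum of one wet episode a week in 10" per cent.

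**The concern.** Two features of the stated text matter.

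- **The effect measure depends on the data.** A Poisson mixed model gives a ratio of weekly rates; a linear mixed model gives a difference in mean accidents. Which of these is the primary result is settled only once the outcome distribution has been seen.
- **The Poisson option carries a strong assumption.** Given the random effects, a child's count may differ from its expected value only by Poisson noise. With a random intercept alone, every child in an arm must also change by the same factor between visits. The protocol expects otherwise: its secondary outcome classifies children as complete, partial or non-responders. If some children become dry while others hardly change, that variation lies within the child across visits, and a random intercept cannot absorb it. The standard error of the month-3 contrast is then too small.

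At stake is the false-positive rate of the main SENS-U versus SHAM test, and its dependence on choices made after the data are in.

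**Working it through.** **1. The plan's own figure.** For 64% versus 79% and "one-sided *a* = 0.05, power = 0.80", Fisher's exact test has power 0.806 at 124 per group, so the stated 124 is reproduced. 160 × (1 − 0.23) = 123.2, so about 123-124 children per arm are expected at 3 months. The sample size is not affected by this point.

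**2. What the Background percentages show.** Treat them as weekly counts of 0 and 1 (an assumption). One common Poisson with P(0) = 0.44 has mean −ln 0.44 = 0.82. Then P(1) = 0.82 × 0.44 = 0.36 and P(>1) = 0.20, against 100 − 44 − 10 = 46% reported. Children therefore differ from each other. That alone is not scatter within a child.

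Could stable differences between children plus one common change explain it? A gamma-Poisson with shape 0.23 and mean 7.6 fits: P(0) = (0.23/7.83)^0.23 = 0.44 and P(1) = 0.23 × (7.6/7.83) × 0.44 = 0.10. If every child had merely halved, the baseline mean would be 15.2 and P(0) = (0.23/15.43)^0.23 = 0.38. It is implausible that 38% of children seeking care for daytime wetting have a dry week at baseline. Unequal response is the more natural reading, but it is an inference.

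**3. Simulation under no effect.** Setting: 124 per arm; visits at baseline, 3 weeks, 3 months and 6 months; arm-by-visit terms; Wald test at 3 months, two-sided 5%; 800 trials per row (Monte Carlo SE about 0.8 to 1.8 points). Assumed: baseline mean about 7 per week, 3-month mean about 2.5, within-child variance μ + kμ². The mixture rows use response classes of 44/10/46%; the simulated share of zero counts at 3 months is then 54-58%, because children who are not fully dry can also have a dry week.

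Rejection rates in %:

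| Assumed scatter | Poisson, baseline covariate, intercept | same + slope | Poisson, baseline as outcome row, intercept | same + slope | Linear (ANCOVA / random intercept) |
|---|---|---|---|---|---|
| k = 0 | 5.1 | 5.1 | 5.0 | 5.2 | 5.8 / 2.9 |
| k = 0.25 | 8.0 | 7.7 | 15.8 | 11.0 | 3.9 / 1.8 |
| k = 0.5 | 12.5 | 12.6 | 29.5 | 18.8 | 4.9 / 1.8 |
| k = 1 | 15.5 | 15.5 | 44.6 | 26.1 | 5.2 / 2.5 |
| k = 2 | 19.3 | 18.5 | 59.6 | 25.4 | 4.9 / 2.0 |
| Responder mixture, Poisson at each visit | 9.8 | 7.4 | 32.6 | 8.8 | 5.6 / 5.8 |
| Responder mixture plus k = 0.5 | 15.8 | 13.4 | 50.6 | 14.7 | 5.4 / 4.3 |

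In the column for baseline as an outcome row with slope, 8 and 201 of 800 fits failed in the two mixture rows.

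The k = 0 row is the control. The 3-month variance-to-mean ratio is 6.13/2.54 = 2.4 across children, yet the test holds its level. Differences between children are harmless; extra scatter within a child is what inflates the test.

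**4. A second set of assumptions.** Setting: 123 per arm; baseline mean 5 (gamma-Poisson, shape 1.5); 33/44/50% dry at 3 weeks, 3 months and 6 months; 25% partial responders; latent correlation between visits 0.7 or 0.9.

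- Baseline as outcome row, intercept only: 30-33%.
- Same with slope: 6.5-9%.
- Baseline as covariate, intercept only: 7-8%.
- Poisson GEE with robust standard errors: 5.6-5.9%.

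In the first case the mean standard error was 0.11 against a true SD of 0.21-0.23. At 0.22 the ratio is 2, and P(|Z| > 1.96/2) = 0.33, which accounts for the rejection rate.

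**5. One-sided 5%,** the only level the article states: about 4-5% at k = 0, and about 6-33% across the overdispersed Poisson cases in the table.

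**The case against.** The strongest reply is that the documents contain no evidence of extra-Poisson scatter within a child. The 44% is a proportion across children, from a meta-analysis, within 1 year rather than at 3 months, and a random intercept exists to absorb differences between children. Without such scatter the test is sound. This stands, and it makes the finding conditional.

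A reader might infer that weekly accidents are known to be far more variable than Poisson, and that the primary test therefore rejects at up to about 30%. The documents do not support that. In the responder mixtures with Poisson scatter at each visit, 30-33% needs two things together: baseline as an outcome row and no random slope. The article lists baseline among the covariates, which most plainly means adjustment, and the slope is planned wherever it can be fitted. Keeping either feature brings the rate down to about 7-10%. Nor is 30% a ceiling: across all the assumptions tried, the range is 5% to 60%. Baseline handling, which drives much of it, is undetailed in the article rather than left to the data. Using every time point, with baseline listed as one, does still permit the outcome-row reading.

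It may also be said that overdispersion terms or robust variances belong in an analysis plan that is not shown. Their absence here is indeed no finding. What remains is what the article does state: two named model families, neither allowing for overdispersion as named, a choice driven by the outcome distribution, and conditional random effects.

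**Conclusion.** The point holds in conditional form and should be fixed. The article lets the data choose between two primary models with different effect measures. Its Poisson option gives standard errors that are too small if children vary between visits by more than Poisson noise. That is plausible given the response classes the protocol expects, but it is not documented.

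At a nominal two-sided 5%, the Poisson option exceeded 5% in every overdispersed scenario tried, while the linear option stayed at or below about 6%. With baseline as a covariate, the plainer reading, the Poisson rate is about 7-10% under responder mixtures with Poisson scatter at each visit, and about 8-19% for k of 0.25 to 2. Higher values depend on entering baseline as an outcome row. All these rates rest on assumed means and dispersions. They show direction and rough size and do not predict this trial's error rate.

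**What to change.** Before the data are seen, name one primary count model that allows overdispersion. Examples are a negative binomial mixed model, or a Poisson mixed model with either an observation-level random effect or child-clustered robust standard errors. Specify arm-by-visit terms, a fixed random-effects structure with a stated fallback for non-convergence, baseline as a covariate, and the sidedness of the test. Name the month-3 SENS-U:SHAM rate ratio as the primary contrast and keep the linear model as a labelled sensitivity analysis. For the primary test, delete the clause that ties the model to the outcome distribution and the clause that makes the random effects conditional on fit.

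The cost is wording only, with no extra children or visits. Confidence intervals will be wider than a plain Poisson model would show. Of the count-model remedies, only Poisson GEE with robust standard errors was simulated here, so the chosen model should be checked in the same way before it is fixed. GEE need not be preferred: with 23% expected loss to follow-up, it generally needs stronger missing-data assumptions than a likelihood-based mixed model.

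### The withdrawal rule reads as last observation carried forward; with 23% planned loss before month 3 it distorts the SENS-U versus SHAM estimate even if loss is equal in both arms

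*Protocol article*

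**What the plan says.** The Data analysis and publication section sets an intention-to-treat analysis, "using a Poisson or linear mixed model (depending on the distribution of the main outcome) with all available study time-points used". The next sentence reads "In case of premature withdrawal, last available data will be used", and nothing limits it to a sensitivity analysis. The section then lists the adjustments: "A correction for baseline, center, age, cumulative dose of antimuscarinics (if applicable), and adherence/drop-out will be performed".

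The endpoint is fixed under Primary outcomes and secondary outcomes: "The main study outcome is the number of wetting accidents per week after 3 months of urotherapy". The visits up to that point are in Study design and setting: "Outcomes parameters are measured at baseline, after the end of 3-week training with or without SENS-U/SHAM, after 3 months at the end of urotherapy". A further assessment follows at 6 months.

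The Sample size section allows for attrition: "With 23% lost to follow-up, we need 160 children per group, 480 children in total".

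**The concern.** A mixed model fitted to all available time-points already accommodates a child who misses the 3-month visit, under missing at random. Keeping the data seen before withdrawal is what that model does by default, so the added sentence has its own meaning only if it puts a value in the place of the missing one.

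Only two visits precede month 3, so only two values can be carried:

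- **Baseline.** This fixes the child's response at zero, whatever was happening at the time of withdrawal.
- **The end-of-3-week assessment.** In the device arms this falls at the end of the wearing period. Carrying it to month 3 assumes that any effect seen then lasts, whereas the trial measures at 3 months to find out whether it does.

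At stake is the primary SENS-U versus SHAM estimate. At the planned loss, nearly a quarter of its 3-month values could be filled in by an assumption of no change after withdrawal.

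**Working it through.** **Inputs from the Sample size section:** success 64% (SHAM) and 79% (SENS-U), one-sided alpha 0.05, power 0.80, Fisher's exact test, 124 per group, 23% loss, 160 per group. The article gives no mean or variance for the weekly count, so the success rates stand in for it, as they do in the plan's own calculation.

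**1. The plan's figure.** The one-sided two-proportion formula with continuity correction gives 123.9, so 124 per group, which matches. Exact one-sided Fisher power at 124 per group is 80.6%. For loss, 124 / 0.77 = 161.04 against 160 stated, which is close enough. The planned loss is 160 × 0.23 = 36.8, about 37 children per group, and 160 × 0.77 = 123.2 are observed.

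**2. Observed data only.** With 123 per group at 64% and 79%, exact one-sided power is 80.2%.

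**3. General form under carry-forward.** Assume equal 23% loss in both arms, unrelated to outcome. Let f be the share of losses that occur before the 3-week assessment. A carried baseline counts as non-success, because no change is no response. Then:

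expected difference = 0.77 × (3-month difference) + 0.23 × (1 − f) × (3-week difference)

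**4. All losses carry baseline (f = 1), planned effect true.**
- SHAM: 0.77 × 64% = 49.3%
- SENS-U: 0.77 × 79% = 60.8%
- Difference: 0.77 × 15 = 11.55, about 11.6 points instead of 15
- Exact one-sided power with all 160 per group counted: 63.3%, against 80.2% in step 2

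**5. All losses carry the 3-week value (f = 0), no true 3-month difference.** Assume 3-week success of 79% versus 64% and 3-month success of 64% in both arms.
- SHAM: 64%
- SENS-U: 0.77 × 64% + 0.23 × 79% = 67.45%
- Spurious difference: 0.23 × 15 = 3.45, about 3.5 points
- Exact one-sided rejection rate with 160 per group: 0.1348, about 13%, against a nominal 5%

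If half the losses fall before week 3 (f = 0.5), the spurious difference halves: 0.23 × 0.5 × 15 = 1.7 points. If all losses come after week 3 and the 3-week difference equals the 3-month difference, the formula gives no bias in the difference.

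**6. Count scale, as a check on direction.** All values here are assumed: baseline mean 7 per week, SD 3, correlation 0.5, loss unrelated to outcome and split evenly before and after week 3, baseline-adjusted comparison, 2,000 runs.
- True 3-month effect −1.0, equal 23% loss: observed cases −1.01, carry-forward −0.89.
- No 3-month effect, 3-week effect −2: observed cases about 0 with type I error about 5%; carry-forward −0.24 with type I error 19%.

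**7. Does the planned drop-out adjustment repair it?** Baseline was carried for all losses, with equal 23% loss and a true effect of −1. The estimate was −0.77 without a drop-out indicator and −0.78 with one, so the shrinkage to about 0.77 of the true effect remains.

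**The case against.** **The sentence may not mean carry-forward.** It could say only that data collected up to withdrawal stay in the analysis. The Sample size section gives this some support: it inflates 124 to 160 as if lost children supply no 3-month outcome, which is unnecessary if outcomes are filled in. Carry-forward is therefore an inference. It remains the natural reading, since the softer one repeats the clause just before it, and on either reading the handling of the primary outcome needs clearer wording.

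**Unequal withdrawal between SENS-U and SHAM is not shown.** A reader might infer it from "The investigator can decide to withdraw a subject from the study for urgent medical reasons, like skin problems". However, the primary contrast is between two devices that the article describes as identical with identical instructions, worn for the same 21 days by children blinded to which one they have. Skin problems and discomfort would be expected in both. The mechanism bears mainly on device versus control, including the secondary SHAM versus control comparison. A figure built on unequal loss is also fragile. With 28% versus 18% loss and an improvement of 3 accidents per week, baseline carry-forward gives (0.28 − 0.18) × 3 = 0.3 accidents per week with no true effect. In simulation this falls to 0.00 once a drop-out indicator is added, and the plan intends some drop-out correction. No such figure is relied on here.

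**A contradiction is too strong a word.** A mixed model can be fitted to filled-in data. The two sentences conflict in method, not in logic.

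**Understated standard errors are not demonstrated.** With equal loss, no true effect and the same 3-week means in both arms, the simulated type I error under carry-forward stayed at 5.2%.

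**The scenarios are extremes.** This is fair: steps 4 and 5 put all losses on one side of the 3-week visit. They bound the problem and do not predict it.

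**Conclusion.** The point holds in this limited form. Read naturally, the rule puts a baseline or end-of-3-week value in the place of the 3-month outcome for up to 23% of children. That can distort the primary comparison with no imbalance in loss at all. It can hide part of a real effect (15 points down to 11.6, power about 80% down to 63%) or create one (3.5 points, type I error about 13% instead of 5%).

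The first result uses the article's own rates and assumes that all losses precede week 3. The second assumes a 79% versus 64% difference at 3 weeks that has vanished by month 3, with all losses after week 3. Both assume that loss is unrelated to outcome and use success rates in place of counts. The direction cannot be settled, because the article does not say when children are expected to leave. A child who leaves after the 3-month visit does not affect the primary outcome. The documents do not support a claim that loss will differ between SENS-U and SHAM.

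**What to change.** Delete the sentence, or replace it with wording such as: all data observed up to withdrawal contribute to the mixed model, and no values are carried forward. State that the primary analysis assumes data are missing at random, and add one sensitivity analysis for departures from that assumption; the method can be left to the statistical analysis plan.

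Where consent allows, keep collecting the weekly accident count at 3 and 6 months from children who stop the device. The Ethical considerations section already provides regular follow-up for those who discontinue, so this is a short added contact.

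The cost is a change of wording, one extra analysis and that contact. The sample size stays at 160 per group, since it was set as if lost children contribute no 3-month outcome.
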